### Sample size

Based on our current experience, an average of 5 patients per month with criteria for neurocritical care are admitted on each center, making a total of 3,240 eligible patients during the 3-year period. Considering a 30% loss due to refusal to consent, non-availability of the research team or missing data, we expect to recruit 2,268 infants from all study centers (around 756 patients per year).

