**Methods:**

A prospective, multicenter, and observational study will be conducted in all 20 Brazilian NICUs using the *PBSF Guidelines* as standard-of-care. All infants treated accordingly to the guidelines during Dec 2021 to Nov 2024 will be eligible. Ethical approval was obtained from participating centers. The primary objective is to describe adherence to the *PBSF Guidelines* and clinical outcomes, by center and over a 3-year period. Adherence will be measured by quantification of neuromonitoring, neuroimaging exams, sub-specialties consultation, and clinical case discussions and videoconference meetings. Clinical outcomes of interest are detection of seizures during hospitalization, use of anticonvulsants, inotropes, and fluid resuscitation, death before hospital discharge, length of hospital stay, and referral of patients to specialized follow-up.

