## Materials and methods

### Study design and setting

This prospective, multicenter, and observational study will be performed in the 20 Brazilian NICU’s located at 4 different states, of which 15 are private and 5 are part of the Brazilian free health care system or phylantropic. All units have adopted the *PBSF Guidelines* as a standard-of-care for high-risk newborns and agreed to participate in the study. Data will be collected for a period of 3 years, from Dec 2021 to Nov 2024.

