Brazil allows several opportunities for telemedicine implementation, expanding the actions of healthcare professionals and integrating healthcare services [86]. We developed the *PBSF Guidelines* with a surveillance and intelligence center to support clinical decisions across the country. Telemedicine has been used by our group in the past few years to promote educational training and remote neuromonitoring but its impact on clinical outcomes needs to be formally evaluated. Thus, results of this 3 years prospective, multicenter, and observational study will help to determine the incidence of neonatal problems associated with brain injury and disabilities, the incidence of clinical and subclinical seizures, detection of brain hemodynamic/oxygenation instability and associated interventions. The study will be limited to the 20 NICUs using the *PBSF Guidelines* and variability in clinical practices, experience of health care providers and staffing of the units, will be analyzed as it may affect some of the outcomes. Enrollment of such large number of patients will require a strong coordination between the central unit and all 20 centers, which has already been established by the CSI. Practical or operational issues will be to assure that all eligible patients are identified in a daily basis and approached for consent. Data collection requires careful training of data extractors and timely and precise data entry. A computerized and safe double-checking system has been developed. Biological signals will be continuously collected and stored at the CSI and multimodal signal analysis has been developed. Although low, there are costs for the implementation and use of the *PBSF Guidelines*. Thus, an adjusted analysis based on the profile of the units will be performed as costs might represent a limitation on the generalizability of the study findings. A future cost/benefit analysis is under planning.

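### The sample-size inputs and total do not agree: 20 centres at 5 infants per month for 36 months gives 3,600 eligible infants, while the protocol states 3,240

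*Protocol article*

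**What the plan says.** The Sample size section gives a monthly rate and a total for all three years in one sentence: "an average of 5 patients per month with criteria for neurocritical care are admitted on each center, making a total of 3,240 eligible patients". It then applies an allowance, "Considering a 30% loss due to refusal to consent, non-availability of the research team or missing data", and concludes "we expect to recruit 2,268 infants from all study centers (around 756 patients per year".

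The other two inputs stand elsewhere in the article:

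- **Number of centres.** The Methods part of the Abstract says the study "will be conducted in all 20 Brazilian NICUs" that use the guidelines. Study design and setting gives the same count and splits it, "of which 15 are private and 5 are part of the Brazilian free health care system or phylantropic". The Discussion repeats it: "The study will be limited to the 20 NICUs".
- **Duration.** Study design and setting says "Data will be collected for a period of 3 years, from Dec 2021 to Nov 2024".

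**The concern.** The Sample size section presents the total as the result of the monthly rate per centre, so a reader should be able to recover it from the rate, the number of centres and the number of months. That is not possible with the values printed. The section is the article's only statement of expected study size, and every later figure in it rests on this first product.

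Two things are at stake, both modest. One is the expected size of the study. The other is the share of eligible infants it expects to lose. Loss here covers refusal of consent, absence of the research team and missing data, and any of these can make the enrolled infants differ from the eligible ones. Data collection and management promises a flow chart of eligible and enrolled infants, overall and per centre. Readers will naturally set that chart beside this forecast, so the forecast should be coherent. If the cause is a different centre count, the discrepancy also bears on how many units contribute.

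**Working it through.** **Inputs**

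| Input | Value | Where |
|---|---|---|
| Centres | 20 (15 + 5) | Abstract, Study design and setting, Discussion |
| Eligible infants per centre per month | 5 | Sample size |
| Months, Dec 2021 to Nov 2024 inclusive | 36 | Study design and setting |
| Loss | 30% | Sample size |

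**Step 1: the stated chain from 3,240 onward.**
3,240 x (1 - 0.30) = 2,268, as stated.
2,268 / 3 = 756 per year, as stated.
Both later steps are computed correctly. Because the three printed figures agree with one another, a misprint or text-extraction fault in a single number is unlikely.

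**Step 2: the first product.**
Eligible = centres x rate x months = 20 x 5 x 36 = 3,600.
Stated: 3,240. Difference: 3,600 - 3,240 = 360, and 360 / 3,600 = 10%.
The stated total is not reproduced. The 30% loss is taken off after 3,240, so it cannot account for the gap.

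**Step 3: what would produce 3,240.** Solving for one input at a time, with the other two as stated:

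- centres: 3,240 / (5 x 36) = 18
- rate: 3,240 / (20 x 36) = 4.5 per month
- months: 3,240 / (20 x 5) = 32.4

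The article states none of these. It describes no staggered start of centres, and Study design and setting says all units have already adopted the guidelines.

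**Step 4: the chain if the stated inputs are right.**

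| Figure | Stated | From 20 x 5 x 36 | Difference |
|---|---|---|---|
| Eligible | 3,240 | 3,600 | 360 |
| Recruited after 30% loss | 2,268 | 3,600 x 0.70 = 2,520 | 252 |
| Per year | 756 | 2,520 / 3 = 840 | 84 |

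On those inputs, 2,268 recruited infants would be 2,268 / 3,600 = 63% of the eligible infants.

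**The case against.** The strongest reply is that the forecast carries little weight. It has no significance level, effect size or precision target. Enrolment ends on a calendar date, all infants treated under the guidelines in that period are eligible, and nothing in the article stops or extends recruitment at 2,268. The stated total is also the lower, more cautious one. All of this stands, and it limits the severity.

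A second reply is that 5 is called an average and may be rounded. If so (an assumption), a rate of 4.5 to 5.49 per month in 20 centres gives 20 x 36 x 4.5 = 3,240 up to 20 x 36 x 5.49 = 3,952.8, with the stated total at the lower edge. This is possible, but the printed rate still does not lead to the printed total. Nor does condensation into an article explain it, since both figures are printed side by side.

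A reader might go further and infer three things that the article does not support:

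- **That 3,240 is the wrong number and the true loss is 37%.** This holds only if 20, 5 and 36 are all right. With 18 centres, or 4.5 infants per month, 2,268 and 756 are correct and the loss is exactly 30%.
- **That the comparisons between years 1, 2 and 3 use wrong denominators.** Outcomes and Statistical methods describe comparisons of data collected in each year, so the denominators will be the infants actually enrolled.
- **That reaching 2,268 would be reported as full attainment of a target.** The article plans no such percentage. The promised flow chart will show the observed enrolment fraction whatever the forecast was.

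**Conclusion.** The point holds as an inconsistency. The number of centres, the monthly rate, the duration and the stated total cannot all be right together. The size of the mismatch is 360 eligible infants, 10% of the 3,600 that the stated inputs give. It carries into the recruited total (252) and the yearly figure (84) if those inputs are right. The calculation counts Dec 2021 to Nov 2024 as 36 full months and assumes that all 20 centres contribute throughout, which is how the article reads. Which input or total is at fault cannot be settled from the article.

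Correcting it restates the expected size, and possibly the implied loss fraction. It changes no outcome, test or eligibility rule. The severity is minor to moderate.

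**What to change.** Reconcile the centre count, monthly rate and total in the Sample size section, and print the product so that it can be checked. There are two routes:

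1. If 20 centres, 5 infants per month and 36 months are right, restate the forecast as 3,600 eligible, 2,520 expected after 30% loss, and about 840 per year.
2. If 3,240 is right, keep 3,240 / 2,268 / 756 and state the input that produces it, such as 18 contributing centres or an average of 4.5 per month. If the centre count changes, bring the Abstract, Study design and setting, and the Discussion into line, or explain there why fewer than 20 centres enter the forecast.

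The first route costs one sentence. The second costs one sentence for a corrected rate, or a few matching edits for a corrected centre count. Neither needs extra patients or any change to the conduct or analysis of the study.

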### Data collection and management

Patient demographics, diagnosis and clinical outcomes will be extracted from the medical charts of each patient and entered in the PBSF database. The *adherence to the PBSF Guidelines* will be measured with the data collected by the *CSI* center. Details of these recordings are provided on S3 Appendix.

A flow chart of all eligible and enrolled patients will be produced, and the total number of patients will be reported, overall and per center.

### Statistical methods

Categorical variables will be analyzed by descriptive statistics and presented as number of valid cases and percentage (%). Numeric variables will be analyzed as mean and standard deviation, median and interquartile ranges, or confident intervals. Since, it is possible that the patient population is quite different across the sites, analyses for the overall population will account for site differences or for the possibility of correlated observations within a site.

To compare adherence and outcomes over time (i.e., between years 1, 2 and 3) the following statistical approach will be applied: a) a test for normality in each category using the Shapiro-Wilks (<50 observations) or Kolmogorov–Smirnov, b) if normality assumption holds, a Welch’s F test will be done, c) if normality assumption still holds the ANOVA with post hoc Bonferroni will be performed. If the normality assumption is violated, a non-parametric test (Kruskal–Wallis) will be used to analyze categorical variables and for significant differences between the two groups (neurological vs clinical). A final *p* value of <0.05 will be considered statistically significant. Analysis of variability (distribution) per site for each variable of the 2 main outcomes will also be performed and Run Chart will be generated to follow the evolution of the outcomes over time for the 2 groups of patients: neurologic and clinical. All analysis will be done using the StataCorp. 2021. Stata Statistical Software: Release 17. College Station, TX: StataCorp LLC.

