### Variables

Population demographics: gender, type of delivery, gestational age at birth, gestational age ≤ 32 weeks and < 37 weeks, Apgar score at 1 min, 5 min and 10 min, birth weight, current weight, inborn or out born, use of antenatal steroids and magnesium sulfate. Primary diagnosis: seizure, mild HIE, moderate or severe HIE/cooling, neurologic abnormalities or congenital central nervous system (CNS) anomalies, grade III or IV intraventricular hemorrhage (IVH) or hydrocephalus, periventricular leukomalacia, meningitis, neural tube defects, stroke, cyanotic congenital heart defect (CHD), prematurity, gestational age ≤ 32 weeks, meconium aspiration syndrome, cardiorespiratory instability (anemia, shock and respiratory alkalosis/acidosis), necrotizing enterocolitis, metabolic disease, extracorporeal membrane oxygenation (ECMO)/pre-ECMO. For descriptive analysis patients will be divided into two groups accordingly to their primary diagnosis: neurological or clinical. A minimal anonymized data set necessary to replicate future study findings is provided as (S4 Appendix).

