### Outcomes

The primary outcomes are detailed on Box 2. Results will be described as n (%) or median [IQR] for the overall population and for each center. Then, we will compare changes over time for the 3 years of data collection within and between centers. Finally, those results will be compared between 2 major groups: neurologic vs clinical patients.

Box 2. Primary outcomes.Adherence to the PBSF GuidelinesUse and duration of aEEG/EEG/NIRS monitoringUse of neuroimaging examsNumber of Sub-specialties consultation (neurology and neurosurgery)Number of primary neurologic or medical patients with aEEG, EEG and/or NIRS monitoring and the duration of the monitoring (hours)Number of primary neurologic or medical patients with brain MRI, neurology consult, and neurosurgery consultNumber of clinical case discussions and videoconference meetingsClinical outcomesNumber of electroencephalographic seizures during hospitalizationUse and types of anticonvulsants administeredUse and types of inotropes and fluid resuscitation administered during NICU stayDeath before hospital dischargeLength of hospital stayNumber of patients referred to high-risk infant follow-up*PBSF, protecting brains and saving futures. *Every attempt will be made to obtain 18–24 months follow-up of these infants, with a Bayley III evaluation.

Secondary outcomes are outlined on Box 3. To address potential source of bias related to financial availability, the outcomes of interest will be also adjusted based on the unit primary profile: private, philanthropic, foundation or public.

Box 3. Secondary outcomes.Descriptive usage of PBSF GuidelinesNumber of remote communications between CSI and local teamNumber of reports issued for aEEG / EEG exams with or without the use of NIRSNumber of patients who performed Therapeutic HypothermiaAdverse effects of brain monitoring expressed by skin lesion due to electrode / sensor positioningPBSF, protecting brains and saving futures; CSI, Central of Surveillance and Intelligence; NIRS, near infrared spectroscopy; aEEG, amplitude integrated electroencephalography; EEG, electroencephalography; MRI, magnetic resonance image; US, ultrasonography.

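### The tests fixed for comparing years 1, 2 and 3 carry no site, cluster or case-mix term, although the same section promises that overall analyses will account for site

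*Protocol article*

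**What the plan says.** All references are to the protocol article.

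- **Statistical methods, first paragraph.** Because "it is possible that the patient population is quite different across the sites", the plan commits that "analyses for the overall population will account for site differences or for the possibility of correlated observations within a site". It names no method for doing so.
- **Statistical methods, second paragraph.** "To compare adherence and outcomes over time (i.e., between years 1, 2 and 3) the following statistical approach will be applied": a normality test, then Welch's F, and then "if normality assumption still holds the ANOVA with post hoc Bonferroni will be performed". If normality fails, Kruskal-Wallis "will be used to analyze categorical variables and for significant differences between the two groups" (neurological and clinical). No site factor, cluster term or covariate appears in the sequence.
- **Outcomes.** Changes over the three years are to be compared within and between centres, and between neurological and clinical patients. The one adjustment variable named is unit profile: "the outcomes of interest will be also adjusted based on the unit primary profile: private, philanthropic, foundation or public".
- **Missing data.** A complete-case analysis is to be followed by likelihood methods, given as mixed effect models. No random effect, covariate or link to the year comparison is stated.
- **Variables.** Gestational age and primary diagnosis are collected, as are "Apgar score at 1 min, 5 min and 10 min, birth weight, current weight, inborn or out born". No stated analysis uses gestational age, birth weight, Apgar score or inborn status for adjustment.
- **Introduction (closing paragraph).** The hypothesis is that adherence will rise over time and that clinical outcomes will improve with it.

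**The concern.** The two paragraphs of Statistical methods do not fit together. The first says overall analyses will respect the clustering of infants in 20 units. The second prescribes, for the main comparison of the primary outcomes, tests that as named treat every infant as an independent observation. Welch's F and Kruskal-Wallis have no place for a site term, and the ANOVA is listed with none.

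Two things are at stake. The first is the error rate: if centres move up or down from year to year, or contribute different shares of infants in different years, the pooled year means vary more than these tests assume. The second is interpretation. There is no control arm, and death, length of stay and drug use depend on how immature and how ill the infants are. A year difference with no patient-level adjustment cannot be separated from a change in who was admitted, and the stated hypothesis invites reading it as an effect of the Guidelines.

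**Working it through.** **Infants per centre-year.** The Sample size section gives 3,240 eligible infants and a 30% loss: 3,240 × 0.70 = 2,268, and 2,268 / 3 = 756 per year. Study design and setting gives 20 centres, so 756 / 20 = 37.8, or about 38 per centre-year. (The 3,240 does not itself follow from 5 per month in 20 centres: 5 × 20 × 36 = 3,600, while 5 × 18 × 36 = 3,240. That is a separate matter. Starting from 3,600 gives 2,520 infants and 42 per centre-year, used below only as a sensitivity check.)

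**Assumptions.** The article gives no intraclass correlation (ICC) and no correlation of a centre's effect between years (CAC). Both are assumed: ICC 0.02 to 0.10; CAC 1 (perfectly stable), 0.8 and 0.5.

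**Formula.** With equal centre sizes, the true variance of a difference between two year means, divided by the variance the named tests assume, is about

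ratio = 1 + (m − 1) × ICC − m × ICC × CAC.

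For three years the test has 2 degrees of freedom, so at a nominal 5% the actual error rate is about 0.05^(1/ratio).

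**ICC 0.05, m = 38.**

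- CAC 1: 1 + 1.85 − 1.90 = 0.95; error about 4.3%
- CAC 0.8: 1 + 1.85 − 1.52 = 1.33; error about 10.5%
- CAC 0.5: 1 + 1.85 − 0.95 = 1.90; error about 20.7%

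**Range over the assumed ICC, m = 38.**

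| ICC | CAC 1 | CAC 0.8 | CAC 0.5 |
|---|---|---|---|
| 0.02 | 0.98 (4.7%) | 1.13 (7.1%) | 1.36 (11.1%) |
| 0.05 | 0.95 (4.3%) | 1.33 (10.5%) | 1.90 (20.7%) |
| 0.10 | 0.90 (3.6%) | 1.66 (16.5%) | 2.80 (34.3%) |

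With m = 42 and ICC 0.05 the ratios are 1.37 and 2.00 (error about 11% and 22%). The conclusion does not depend on which accrual figure is used.

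**Check by simulation.** ANOVA, Welch's F and Kruskal-Wallis were run on 20 centres averaging 38 infants per centre-year, with no true year effect and 1,000 runs per setting. The three tests behaved alike. Error rates for ICC 0.02, 0.05 and 0.10:

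- Stable centre effects and enrolment shares: about 4 to 7% throughout, so no material inflation.
- Half the centre variance changing by year (CAC 0.5): about 10%, 22 to 24%, and 33%, in line with the formula.
- Stable centre effects but drifting enrolment shares (standard deviation of centre trends 0.5 log units per year): about 7 to 8%, 14% and 23%.
- Both together: about 13 to 15%, 28 to 29%, and 48 to 50%.

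**Case mix alone.** Assume mortality is 20% in high-risk and 5% in lower-risk infants in every year, with 756 infants per year and no change in care. If the high-risk share is 50%, 40% and 30%, overall mortality falls from 0.20 × 0.50 + 0.05 × 0.50 = 12.5%, through 11.0%, to 0.20 × 0.30 + 0.05 × 0.70 = 9.5%. A three-year chi-square test (for a yes/no outcome, practically the same as Kruskal-Wallis) was significant in about 37% of 4,000 simulated studies. With shares of 50%, 45% and 40% it was about 10%, and with no shift about 5%.

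**Whether another section repairs this.** The mixed effect models could hold a centre effect, but they are placed under missing data and not tied to the year comparison. Unit profile is a funding category, so it stands for neither the individual centre nor the patient. The neurological/clinical split is a coarse form of case-mix handling, but gestational age and severity still vary within each group, and it adds no site term.

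**The case against.** The case against is substantial. The stated aim is descriptive. The article names mixed effect models, separates neurological from clinical patients, adjusts for unit profile, and says in the Discussion that variability in practice and staffing will be analysed. ANOVA can in principle take a site factor. A full covariate list is commonly left to an analysis plan or the full protocol, neither of which is shown. The inflated error rates rest on assumed correlations and vanish when centres and enrolment shares are stable.

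Much of this limits the point without removing it. The article does not leave the year comparison open: it fixes the tests, two of them cannot hold a site term, and the only suitable model is assigned to another task. The hypothesis linking adherence to better outcomes also goes beyond description.

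Four stronger readings are tempting but not supported:

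- *Centre-to-centre comparisons use the same tests.* The sequence is written for years 1 to 3, with Kruskal-Wallis also for neurological and clinical groups. Per site, only an analysis of distributions is assigned.
- *Missing patient-level adjustment contradicts the promise.* The promise concerns site or within-site correlation, and differing patients are only its reason. Missing case-mix terms are a weakness of the chosen tests, not a contradiction.
- *Standard errors for private against non-private units will be far too small, or profile will clash with fixed centre effects.* The setting is described as 20 units, "of which 15 are private and 5 are part of the Brazilian free health care system or phylantropic", but the plan announces adjustment for profile, not a test of that contrast, and specifies no fixed centre effects.
- *The error rate will be inflated.* It will be only if centre effects or enrolment shares move between years.

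**Conclusion.** The point holds for the year-to-year comparison. As written, the named tests cannot deliver the accounting for site that the preceding paragraph promises, and no other section supplies it. The size is conditional: at an assumed ICC of 0.05 the error rate is roughly 10 to 20% for between-year centre correlations of 0.8 to 0.5, and close to the nominal 5% when centre effects and enrolment shares are stable. Confounding by a shift in patient mix is a separate weakness of the same tests. It matters because the hypothesis ties rising adherence to better outcomes, but its size cannot be known in advance. The conclusion does not extend to between-centre tests or to a comparison of funding profiles.

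**What to change.** 1. For infant-level outcomes, replace the one-way tests for the year comparison with one regression suited to the outcome type: a mixed model, or GEE with a small-sample correction for 20 centres. Year is the effect of interest and centre the cluster, with centre-by-year variation allowed.
2. Prespecify a short list of case-mix covariates from those in the Variables section, for example gestational age and primary diagnosis group.
3. Analyse centre-level counts, such as case discussions and videoconference meetings, at centre level, where infant covariates do not apply.
4. Reconcile Outcomes, Statistical methods and Missing data, so that the mixed models now listed for missing values and the model for the year comparison are stated as one plan, with the role of unit profile in it.

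The example covariates are already collected, so no new data are needed. The cost is a change of analysis wording, slightly more analysis work and possibly wider intervals.

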The aim of this prospective multicenter and observational study is to describe the centers’ adherence to the *PBSF Guidelines* and clinical outcomes over a 3-years period. We hypothesize that the adherence to the *PBSF Guidelines* will increase over time and this will be associated with improvement of clinical outcomes. Results of this study may provide the necessary background information on the use of telemedicine aiming to protect neonatal brains and save futures, and for the development of larger studies and initiatives.

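### The tests named for years 1, 2 and 3 ignore the order of the years, so a significant overall result does not by itself show the hypothesised increase in adherence

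*Protocol article*

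**What the plan says.** The last paragraph of the protocol article's Introduction gives a directional hypothesis: adherence to the guidelines "will increase over time and this will be associated with improvement of clinical outcomes". The abstract frames the main aim differently: "The primary objective is to describe adherence to the" guidelines and the clinical outcomes, by center and across three years.

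Statistical methods fixes how time is analysed. The comparison is introduced with "To compare adherence and outcomes over time (i.e., between years 1, 2 and 3". The sequence is a normality check, then "if normality assumption holds, a Welch’s F test will be done", then "ANOVA with post hoc Bonferroni will be performed". If normality fails, "a non-parametric test (Kruskal–Wallis) will be used to analyze categorical variables". The same section adds that a "Run Chart will be generated to follow the evolution of the outcomes over time" in the neurologic and clinical groups.

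No trend test, linear contrast or regression on time is named. Mixed effect models appear only under Missing data, as a way of handling incomplete records and without a time term. Sample size gives an expected 756 infants per year but no effect size, SD, adherence rate or power.

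**The concern.** The hypothesis has a direction and the overall tests do not. Welch's F, one-way ANOVA and Kruskal–Wallis across three years spread their sensitivity over any difference among the three groups. Two things are at stake. First, interpretation: p < 0.05 from such a test could come from a fall, or from year 2 alone, so it cannot be reported as confirming an increase. Second, efficiency: when the rise is roughly linear, a 2-df test detects it less often than a 1-df test aimed at trend. This is not detail left open for a later analysis plan, because the article names the tests.

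**Working it through.** **Inputs.** From Sample size: 756 infants per year. From Statistical methods: three yearly groups and a 0.05 threshold. Assumed here, because the protocol gives none: a two-sided test, the adherence rates, effects in SD units, the shape of the rise, and any design effect for clustering by site.

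**The plan's own figure.** 3,240 × 0.70 = 2,268 and 2,268 / 3 = 756, as stated. The starting 3,240 equals 5 × 18 centers × 36 months; with the 20 centers described it would be 3,600. That is a separate matter and does not affect the comparison of tests below.

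**What each planned element says about direction.**
- Welch's F, the ANOVA F test and Kruskal–Wallis: unchanged if the year labels are permuted, so none.
- Bonferroni contrasts: year 3 minus year 1 has a sign, but the contrasts are attached only to the ANOVA, and each of the three is tested at 0.05/3. No post hoc test is named after Kruskal–Wallis.
- Run chart: keeps time order, with no test or estimate attached.

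**Power, general result for a linear rise.** Power is the probability that a noncentral chi-square with noncentrality λ exceeds 3.841 (1 df) or 5.991 (2 df). For a linear rise both tests share the same λ.
- λ = 7.849: 80.0% (1 df), 70.9% (2 df).
- λ = 10.507: 90.0% (1 df), 83.5% (2 df).
- The 2-df test needs λ = 9.635 for 80%. The ratio 9.635 / 7.849 = 1.23 means about 23% more infants.

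**Binary illustration, n = 756 per year, infants treated as independent.** With p̄ the mean of the three rates:
- λ(trend) = n (p3 − p1)² / [2 p̄(1 − p̄)]
- λ(overall) = n Σ(pi − p̄)² / [p̄(1 − p̄)]

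For 60/63.5/67%: p̄(1 − p̄) = 0.635 × 0.365 = 0.2318, and both λ = 756 × 0.00245 / 0.2318 = 7.99. For 60/67/67%: p̄(1 − p̄) = 0.2285, λ(trend) = 756 × 0.0049 / (2 × 0.2285) = 8.11, and λ(overall) = 756 × 0.003267 / 0.2285 = 10.81.

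| Assumed rates, years 1/2/3 | Shape | Trend, 1 df | Overall, 2 df |
|---|---|---|---|
| 60/63/66% | linear | 68% | 57% |
| 60/63.5/67% | linear | 81% | 72% |
| 60/65/70% | linear | 98% | 96% |
| 60/65/67% | slowing | 81% | 75% |
| 60/66/67% | nearly flat after year 2 | 81% | 79% |
| 60/67/67% | one step | 81% | 85% |

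**Continuous illustration, n = 756 per year, linear rise of d SD from year 1 to year 3, λ = n d² / 2.**
- d = 0.144: trend 80.0%, ANOVA 70.8%, Bonferroni year 1 vs 3 65.8%.
- d = 0.20: trend 97.3%, ANOVA 94.5%, Bonferroni year 1 vs 3 93.2%.
- d = 0.144 reached wholly by year 2: trend 80.0%, ANOVA 83.3%.

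**Clustering.** If site correlation halved the effective number (an assumption), 60/63.5/67% gives 52% against 42%. For 60/65/70%, λ = 378 × 0.005 / 0.2275 = 8.31, which gives 82% against 73%. The gap then returns at effect sizes where it was negligible under independence.

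**The case against.** The strongest reply is that the loss depends on a shape the protocol never states. A reader might infer that the hypothesis is a steady rise and that the planned tests therefore waste power. The Introduction speaks only of an increase over time. A plateau after an early gain fits that wording, and is plausible because the units had already adopted the guidelines before data collection. In that case the overall test does slightly better. A claim that any monotone rise is detected less often would therefore be wrong: 60/67/67% never falls, and the 2-df test detects it more often.

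A reader might also infer that the study is underpowered for its question. The documents do not support that either: the stated primary objective is descriptive and no power target exists to be missed. The planned tests are not invalid for ignoring order; ignoring it does not raise the type I error. In the ANOVA branch the post hoc contrasts partly answer the question of direction, and a significant linear slope does not prove that every step was upward.

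These points limit the size of the concern and all of them stand. What they leave untouched is the mismatch. The protocol states a directional hypothesis and a significance threshold, and no named analysis tests direction when the Kruskal–Wallis branch applies. The site adjustment it promises could carry a time term, but none is named.

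**Conclusion.** The point holds in a limited form. The tests named for the three years do not match the directional hypothesis, and a significant overall result should not be read as an increase. The efficiency cost is conditional: about 9 to 10 points of power near 70–80% for a roughly linear rise (about 23% more infants to match 80%), 2 to 3 points or less for larger effects under independence, and a reversal of about 3 points for a single-step rise. The absolute powers rest on assumed rates and SDs, a two-sided 0.05 test and 756 infants per year. Clustering would lower them and make the gap relevant at larger effects. This is a change worth making, not a flaw that invalidates the planned comparison.

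**What to change.** In Statistical methods, name one ordered-time analysis as the test of the hypothesis in the Introduction: a linear term for year or calendar month in a site-adjusted model, reported as a slope with its confidence interval. If simple tests are kept, use Cochran–Armitage for binary variables and Jonckheere–Terpstra for continuous or ordinal ones. Retain the 3-group comparison as a supportive check for plateau or non-monotone patterns, and state that its overall p value alone will not be taken as evidence of an increase.

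The cost is wording only, with no new data or patients. The downside is slightly lower power if the rise is a single step (about 3 points in the examples) and lower sensitivity to a non-monotone pattern; the retained 3-group test covers both.
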